### Prior and concomitant treatments

Relevant additional treatments administered to the subjects on entry to the trial or at any time during the trial are regarded as concomitant treatments und are documented on the appropriate pages of the case report form (CRF). TAU is allowed in the intervention as well as the control group. TAU includes stable psychopharmacotherapy, stable medication for chronic medical conditions not interfering with group therapy, individual language, psychomotor or behaviour therapy, personal support at school or family support. Kind and frequency of TAU in the treatment and control groups will be compared for non-random distribution in the statistical analysis.

Psychotropic medication is started or changed at least four weeks before randomisation and remains stable (mg/kg body weight) throughout the intervention and the three months follow-up of the study (with the exception of dose adjustment to body weight changes). The following psychotropic medication is allowed as single or combined treatment: SSRI, other antidepressants, typical or atypical neuroleptics, stimulants, atomoxetine, or mood stabilisers. In addition, stable medication for the treatment of chronic conditions such as allergies, asthma, epilepsy, enuresis, sleeping problems, and intermitting medication for acute upper respiratory infections and diarrhoea is allowed. Pharmacological treatment is documented at each time of assessment (T1-T5), and effects of psychotropic medication on treatment outcome will be explored in the statistical analysis.

Any individual intervention (for example, cognitive behavioural therapy, school-based intervention, occupational, language, psychomotor therapy) or family-based intervention is also allowed. Any additional treatment is documented in detail (kind of intervention, dose, frequency, etcetera).

### Intervention

SOSTA-FRA is manualised, structured cognitive-behavioural therapeutic and group-based social skills training for children and adolescents with ASD. It combines psycho-educational, experimental, and operant methods of teaching and practising social skills. The groups are lead by two trained behavioural psychotherapists. Twelve sessions, each of 90 minutes duration, are provided. Each session follows a standard sequence of activities: saying hello/greeting, opening round with group circuit and repetition of group-rules, session specific topic (which consists of the introduction of new skills followed by the respective training), group game, homework and closing round with feedback. The following social skills are taught, discussed, and practised within the 12-week curriculum: establishing group rules, using eye contact, introducing oneself to others, awareness and expression of feelings, non-verbal communication, politeness, listening, getting into contact with peers, having fun being part of a social group, apologising, conversational skills, negotiation, dealing with teasing/bullying, making friends, problem solving, self-regulation, impulse control, and strategies for coping with anger. Thus, SOSTA-FRA takes on the essential topics and methods that have been recommended for ASD-specific SST as delineated in the introduction section (aiming at increasing social motivation and social initiations, improvement of appropriate social responding, improvement of executive functions, reduction of interfering behaviours and promotion of skill generalisation by social learning and operant methods, as well as cognitive approaches). Every session includes homework to ensure transfer and generalisation of acquired skills. The last session includes a group activity outside the clinical setting. SOSTA-FRA implements a token program for the single session and for homework, and therapists provide extensive positive reinforcement of response attempts, of appropriate responses, and of use of acquired skills.

Accompanying the group-based intervention or during the waiting time of the control group, three parent training sessions, each of 90 minutes duration are additionally provided for the intervention and the control group. The aim of the parent training sessions is to ensure compliance, educating parents with regard to ASD in a general way, supporting parents to cope with their children, increase support between families, giving parents the opportunity to talk about current issues and aspects of their children, and to obtain the study questionnaires on a regular basis.

### Assessment

The trial time flow is shown in Figure 1. After verifying the diagnosis of HFASD and screening for eligibility (T1), ten individuals are included in an age-homogenous study group. The participants are then randomised to the intervention and control group, and the baseline assessment (T2) takes place. Following randomisation, the first parent training (both for parents of the children in the intervention and the control group) and the first SST group session of at least five individuals are performed. Mid-intervention assessment takes place after 6 weeks group training, parallel with the second parent training. This mid-intervention assessment (T3) aims at obtaining the primary and secondary outcome measures during the ongoing trial to get some information on individuals dropping out from the study before T4. One week after the last group SST session, the third parent training is provided and post assessment takes place (T4). To assess the stability of the therapy effects, the study also includes a follow-up (T5) measurement 3 months after finishing the SST.

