### Outcome measures

The primary outcome measure is the parent-rated Social Responsiveness Scale (SRS) which was developed as a change-sensitive measure of social abilities [16,17]. It contains 65 items covering social responsiveness and interaction, communication and stereotyped behaviours in children and adolescents. Five subscales (social awareness, social cognition, social communication, social motivation and autistic mannerisms) and a summary score can be calculated. Change in the total raw score of the Social Responsiveness Scale (SRS) as assessed by the primary caretaker (PC) (a) between baseline (T2) and 12 weeks after baseline (T4) (primary endpoint), as well as (b) between baseline (T2) and 3 months after the end of the intervention (T5) (co-primary endpoint) is the primary outcome measure in this study. The parent-rated SRS has been chosen as the outcome measure in several studies on SST in HFASD [9,12,14].

The secondary outcome measures aim to differentially assess aspects of social interaction, psychopathology, depressive and anxious symptoms. All secondary outcome measures have been validated and are frequently used in clinical research in child psychology and psychiatry. Some of these secondary outcome measures have not been standardized for individuals above 16 or 18 years of age. However, as changes in raw scores are used as secondary outcome measures in this study, the reported scales are considered as valid measures. The following secondary outcome measures will be assessed directly after therapy and 3 months after the end of intervention:

1. Response to intervention: individual symptom reduction of at least 16 raw points (1 SD) in PC-rated SRS total score

2. Teacher (T)-rated SRS (change in total raw score and response to intervention, that is, reduction of at least 16 raw points in the T-rated SRS)

3. Change in the SRS subscale raw scores in PC, T-rated SRS

4. Change in PC-rated anxious-depressive symptoms – raw score as assessed by the child-behavior checklist (CBCL). The CBCL is a parent rating scale with 120 Likert (0 to 3)-coded items to assess psychopathology in different aspects of behaviour [18]. In this study, the anxious-depressive subscale raw score (14 items) is chosen, as individuals with HFASD often suffer from comorbid anxiety and depressive disorder, possibly related to their problems with social interaction

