### Methods against bias

To randomly allocate influencing factors and to avoid selection bias, patients are randomly assigned by centralised randomisation to each group (intervention group and wait-list/TAU control group). An internet-based randomisation system (http://randomizer.at) is used. The randomisation is done in an allocation ratio of 1:1 with variable block length and is stratified for each participating centre.

To ensure that all participating centres will implement the SST and parent training in a very comparable way across centres, all therapists are trained in the SOSTA-FRA program before the beginning of the study in their centre. Further, all therapists are supplied with a detailed written manual including all performance rules. Regular telephone supervision and meetings are provided. In addition, one therapy session of each intervention group is videotaped and analysed for compliance with the manual by independent raters at the Frankfurt study centre. Reliability training in diagnostic measures has been performed before the start of the study.

As the proposed study is a behavioural therapy intervention study, blinding of participants as well as therapists or parents is not possible. Teachers are blinded to intervention. Therefore, a possible bias of the SRS-parent scores can be detected by comparing it to the SRS-teacher scores. The teacher scores, however, will not be used as primary outcome measure, as it is to be expected from previous studies [22] that return of teacher questionnaires will only be around 50 to 60%. Independent clinical on-site monitoring to ensure patient safety and integrity of the clinical data in adherence to the study protocol focuses on source data documentation, correctness of data, and adherence to trial procedures, for example, randomisation and treatment.

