### Statistical analysis

Confirmatory analysis is performed for the ITT population, and is defined on the basis of the ITT principle. An additional per-protocol analysis will be conducted, which will include all patients without major protocol violations. Two primary endpoints are assessed in confirmatory analysis, namely the change in SRS total score between baseline and 12 weeks after baseline (effect at the end of therapy) and the change in SRS total score between baseline and three months after the end of therapy (maintenance effect). To ensure control of the multiple type I error rate at 5%, a hierarchical test procedure will be applied [23]: The first null hypothesis to be tested states that the change in SRS total score between baseline and 12 weeks after baseline is equal for both groups. If this hypothesis can be rejected at the two-sided significance level of 5%, the second null hypothesis stating that the change in SRS total score between baseline and three months after the intervention is equal in both groups is tested at the two-sided level 5%. If the first null hypothesis cannot be rejected, the second null hypothesis referring to the co-primary endpoint is also accepted.

Both null hypotheses will be tested by analysis of covariance with the covariates baseline SRS total score, age, IQ, and centre. Gender and medication effects were not observed in previous studies [14], and hence these variables are not included in the model of the primary analysis. Missing values with respect to post-baseline primary outcomes will be handled by application of the mixed-effects model for repeated measures (MMRM) approach that turned out to show favourable characteristics in terms of the type I error rate, power, and bias of estimates as compared to alternative methods dealing with missing values, such as last-observation-carried-forward (LOCF) [24-26].

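### The baseline SRS is placed after randomisation and rated by caretakers who cannot be blinded; unless it is completed before allocation is disclosed, the reference value for both primary endpoints is open to bias

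*Protocol article*

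**What the plan says.** The Assessment section sets out the sequence. First comes T1: "After verifying the diagnosis of HFASD and screening for eligibility (T1), ten individuals are included in an age-homogenous study group". Then: "The participants are then randomised to the intervention and control group, and the baseline assessment (T2) takes place". The first parent training and the first group session follow. No SRS is described at T1.

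Under Outcome measures, the primary outcome is "Change in the total raw score of the Social Responsiveness Scale (SRS) as assessed by the primary caretaker (PC"). It is taken "between baseline (T2) and 12 weeks after baseline (T4) (primary endpoint") and "between baseline (T2) and 3 months after the end of the intervention (T5) (co-primary endpoint"). Under Statistical analysis, both hypotheses are tested by ANCOVA with baseline SRS, age, IQ and centre as covariates.

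Methods against bias states that "blinding of participants as well as therapists or parents is not possible". It names one check on parent-rating bias, a comparison with SRS scores from blinded teachers, and expects about 50 to 60% of teacher questionnaires back. The Intervention section adds that the parent trainings serve, among other aims, "to obtain the study questionnaires on a regular basis". The control arm waits six months for the same training.

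**The concern.** Adjusting for baseline is safe when the baseline cannot have been affected by the assignment. A measurement taken before randomisation, or before anyone concerned knows its result, meets that condition by design. A rating made afterwards by an unblinded parent does not. A parent who has just learned of an immediate place, or of a six-month wait, may rate the child's difficulties differently for that reason alone.

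Such a reaction would create a difference between arms in T2 that is not a chance imbalance. The ANCOVA would nonetheless correct for it as if it were one, and the correction would move the treatment estimate. Both confirmatory tests use the same T2 value. The caretaker-rated responder outcome and the other unblinded change scores measured from T2 share the exposure.

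**Working it through.** **Inputs from the Sample size calculation section.** Difference 11 points, SD 28, two-sided 5%, power 80%, 103 evaluable per arm.

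**Assumed inputs.** The article gives neither of these:
- b, the difference between arms in T2 caused by knowledge of allocation: 1, 3 or 5 points.
- β, the within-arm slope of follow-up SRS on T2: 0.6 to 0.8. With equal variances at the two times, β equals the correlation.

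**The plan's own figure.** An exact two-sample t-test with difference 11 and SD 28 needs 103 per arm (power 80.1%), so the stated 206 reproduces. The standard error without adjustment is 28 × √(2/103) = 3.90.

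**Standard error under ANCOVA.** If 28 is the SD of the change, the SD at one time point is s = 28/√(2(1−β)). The residual SD is s√(1−β²) = 28√((1+β)/2).
- β = 0.6: residual SD 25.0, SE = 25.0 × √(2/103) = 3.49
- β = 0.8: residual SD 26.6, SE = 26.6 × √(2/103) = 3.70

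**Bias.** The ANCOVA estimate is (difference at follow-up) − β × (difference at T2). It is the same whether the outcome is the change or the follow-up score.
- If b is present at T2 and gone by T4/T5, the bias is −β × b.
- If b persists unchanged, the bias is b − β × b = (1−β) × b, with the opposite sign.

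**Shift gone by follow-up.** Rejection rates under no true effect come from the noncentral t with 103 per arm:

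| b (assumed) | Bias, β 0.6 to 0.8 | Share of 11 points | Type I error |
|---|---|---|---|
| 1 | 0.6 to 0.8 | 5 to 7% | 5.3 to 5.5% |
| 3 | 1.8 to 2.4 | 16 to 22% | 8.1 to 9.9% |
| 5 | 3.0 to 4.0 | 27 to 36% | 13.7 to 18.9% |

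If a 3-point shift works against the intervention, power at a true 11-point effect falls from 84–88% to 64–75%.

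**Shift that persists.** For b = 3 the bias is (1−0.8) × 3 = 0.6 to (1−0.6) × 3 = 1.2 points in the other direction.

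**Could a T2 comparison between arms detect it?** With s = 31.3 (β = 0.6) to 44.3 (β = 0.8), the SE of a T2 difference is 4.4 to 6.2. With the 16 raw points that Outcome measures calls 1 SD, it is 16 × √(2/103) = 2.2. A 3-point difference is at most 3/2.2 = 1.4 standard errors, so it could not be told from chance.

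**The case against.** The strongest reply is that the article does not say when families learn their allocation. Randomisation is central, so generating an allocation and disclosing it can be separate steps. The time-flow figure, which might settle this, is not shown in the text at hand. This stands. A reader might infer that T2 ratings were in fact made with knowledge of allocation; the article supports only that they could have been. The parent-training remark does not close the gap. The Assessment section ties T3 to the second training and T4 to the third, but does not tie T2 to the first.

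A reader might also quote the full shift as the bias: 3 points, or 27% of the planned effect, with a type I error near 12%; for 5 points, 45% and near 25%. Those figures belong to an unadjusted change score. The planned test is ANCOVA, which removes part of a transient shift, so only the smaller figures in the table apply.

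A third inference would be that families left between allocation and T2, so that the ITT analysis is compromised. The sentence "Missing values with respect to post-baseline primary outcomes will be handled" covers only values after baseline. But the article gives no sign of such losses, and the handling of missing baselines is a detail that a condensed article leaves to the full protocol or analysis plan. It is not part of this point.

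Finally, the blinded teacher SRS is a real safeguard, but only a partial one. About half the ratings are expected, and secondary outcomes are analysed descriptively.

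**Conclusion.** The point holds as a weakness of design that should be fixed. As written, the plan puts the reference value for both primary endpoints after randomisation, in the hands of an unblinded rater, without stating that it is completed before disclosure. This is not a matter of brevity, because the article itself states the order.

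The size is unknown. Under a shift that is gone by follow-up, the bias runs from negligible (1 point) to about a quarter to a third of the planned effect (5 points). A persistent shift gives a smaller bias in the opposite direction at these slopes. The shifts and slopes are assumptions, and the calculation treats the primary analysis as a simple ANCOVA with complete data. Nothing in the article shows that a bias occurred, and the sample size is unaffected. If T2 did precede disclosure, what remains is a description to correct.

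**What to change.** 1. For children still to be randomised, obtain the T2 parent and self-report questionnaires before the allocation is generated or disclosed. Teacher questionnaires need not move on this ground, since teachers are blinded. By October 2012, 204 of 220 had been randomised, so this step reaches about 16 children (7%). The next two steps therefore matter more.
2. For those already randomised, record whether T2 preceded disclosure. Report T2 SRS by arm descriptively, and do not read a small difference, or the lack of one, as evidence either way.
3. Pre-specify a sensitivity analysis of T4 and T5 SRS that omits T2 and adjusts only for variables fixed before randomisation: ADOS/ADI-R severity, IQ, age and centre.
4. If the records show that T2 preceded disclosure, correct the order given in the Assessment section.

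The cost is an earlier questionnaire, a check of dates and one extra analysis, with no added visit. The drawback is that the sensitivity analysis is less precise without T2, so it should support the primary ANCOVA and not replace it.

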**Figure 1 F1:**
[figure not shown]
Trial Time Flow.

### Outcome measures

The primary outcome measure is the parent-rated Social Responsiveness Scale (SRS) which was developed as a change-sensitive measure of social abilities [16,17]. It contains 65 items covering social responsiveness and interaction, communication and stereotyped behaviours in children and adolescents. Five subscales (social awareness, social cognition, social communication, social motivation and autistic mannerisms) and a summary score can be calculated. Change in the total raw score of the Social Responsiveness Scale (SRS) as assessed by the primary caretaker (PC) (a) between baseline (T2) and 12 weeks after baseline (T4) (primary endpoint), as well as (b) between baseline (T2) and 3 months after the end of the intervention (T5) (co-primary endpoint) is the primary outcome measure in this study. The parent-rated SRS has been chosen as the outcome measure in several studies on SST in HFASD [9,12,14].

The secondary outcome measures aim to differentially assess aspects of social interaction, psychopathology, depressive and anxious symptoms. All secondary outcome measures have been validated and are frequently used in clinical research in child psychology and psychiatry. Some of these secondary outcome measures have not been standardized for individuals above 16 or 18 years of age. However, as changes in raw scores are used as secondary outcome measures in this study, the reported scales are considered as valid measures. The following secondary outcome measures will be assessed directly after therapy and 3 months after the end of intervention:

1. Response to intervention: individual symptom reduction of at least 16 raw points (1 SD) in PC-rated SRS total score

2. Teacher (T)-rated SRS (change in total raw score and response to intervention, that is, reduction of at least 16 raw points in the T-rated SRS)

3. Change in the SRS subscale raw scores in PC, T-rated SRS

4. Change in PC-rated anxious-depressive symptoms – raw score as assessed by the child-behavior checklist (CBCL). The CBCL is a parent rating scale with 120 Likert (0 to 3)-coded items to assess psychopathology in different aspects of behaviour [18]. In this study, the anxious-depressive subscale raw score (14 items) is chosen, as individuals with HFASD often suffer from comorbid anxiety and depressive disorder, possibly related to their problems with social interaction

5. Change in total, pro-social behaviour and peer-related problems raw scores as assessed by the Strength and Difficulties Questionnaire (SDQ: PC, T-rated). The SDQ is a widely used, German-translated and validated instrument [19] and includes subscales of conduct, emotional, hyperactivity and peer-related problems, as well as pro-social behaviours

6. Change in self-reported depressive symptoms as assessed by the *Depressionsinventar für Kinder und Jugendliche* (DIKJ). The DIKJ is a self-reported scale for children and adolescents 8 to 16 years of age and contains 26 Likert (0 to 3)-coded items [20]

7. Qualitative information on motivation and satisfaction with therapy (self-assessment)

8. assessment of functional genetic variants and psychotropic medication as possible moderating variables of therapeutic effect;

9. change in electrophysiological brain activation during the processing of social stimuli. EEG based evoked potentials to emotional faces and Mu oscillations to biological motion patterns to study neural change induced by SST are obtained at T2, T4 and T5 at the Frankfurt study site, aiming at including 25 HFASD individuals from the treatment and 25 HFASD from the control group.

### Sample size calculation

The sample size calculation refers to the primary endpoint, change in SRS total score between baseline and 12 weeks after baseline, in the ITT population. The prior assumption for the treatment effect of the experimental intervention is based on the results of Tse *et al*. (2007) with a treatment mean difference of 11 points and SD of 28 points. It is assumed that the mean SRS total score does not change for the control group and that the same SD as in the experimental intervention holds true. With a two-sided significance level of α = 5% and a power of 1-β = 80%, a sample size of 206 (2 × 103) is required to detect this difference with a two-sample *t*-test. It can be expected that application of an analysis of covariance as defined for the evaluation (see below) will reduce the SD, thus increasing the actual power of the study. Based on the observations made in the study of Tse *et al*. (2007), the dropout rate during the intervention is assumed to be about 5%. Therefore, 220 individuals will be randomised in total, to obtain at least 206 evaluable patients. On the basis of the information from the clinical study centres, it is expected that about 25% of the screened patients cannot be included in the study due to violation of the inclusion/exclusion criteria. Hence, 300 patients will be assessed for eligibility. Sample size calculation was done using nQuery Advisor 7.0 [21].

